## Abstract

**Background:**

Cardiorenal anemia syndrome (CRAS) is a common complication among patients with heart failure and is associated with poor clinical outcomes. However, there is a paucity of published data concerning CRAS, despite of significant increase in heart failure patients attending medical services in developing countries. This study aims to assess the prevalence, clinical correlates, and outcomes of CRAS among patients with heart failure attending the Benjamin Mkapa Hospital in Dodoma, Tanzania.

**Methodology:**

A prospective observational study is ongoing at the Benjamin Mkapa Hospital in Dodoma, Tanzania. Currently, 92 patients have been recruited into this study and process is not yet completed. The socio-demographic data, clinical correlates, and prevalence of CRAS will be determined at baseline meanwhile, the outcomes of CRAS will be determined during a follow-up period of six months from the date of enrollment. CRAS is the primary outcome of the study. Data will be categorized into CRAS and non-CRAS during statistical analysis. Mean and standard deviation will be used for normally distributed continuous variables while median and interquartile range will be used for skewed data. Frequencies and percentages will summarize categorical variables. Clinical correlates and outcomes of CRAS will be analyzed and compared by using univariate and multivariate logistic regression and Cox proportional hazards models. A two-tailed p-value of less than 0.05 will indicate statistical significance.

## Introduction

Cardiorenal anemia syndrome (CRAS) is public health concern worldwide among heart failure patients and is associated with poor clinical outcomes [1, 2]. The pathophysiology of cardiorenal anemia syndrome is complex and not clear [2–4]. The reported prevalence of CRAS among heart failure with reduced ejection fraction ranges 4.6% and 35.4% in developed countries [5–7] and 19% to 66% in developing countries [2, 5].

CRAS management poses great challenging due to increased cost of services and disease-drug interactions, which portends poor prognosis [1, 2, 8] which explains a very high CRAS related mortality in developing countries (73.5%) than in developed countries (9.5%) [1, 2, 9]. There are several clinical correlates which have been reported to contribute the development and worsening of CRAS including among others diabetes, hypertension, dyslipidemia, obesity, alcoholism and iron deficiency with or without anemia but all these correlates have not yet been established in our settings [5, 10–12]. The most common outcomes of CRAS include all-cause mortality, poor quality of life, heart failure hospitalization, worsening anemia and worsening renal function [1, 2, 13].

There is a significantly increasing burden of HF patients in Tanzania. In our settings, approximate 20 to 50 patients with heart failure attend daily in respective clinics; however, there is unpublished data from hospital registries pertaining to cardiorenal anemia syndrome [5, 8, 14]. This study is the first to be conducted in our settings and will determine the prevalence, clinical correlates and outcomes of cardiorenal anemia syndrome among the patients with heart failure irrespective of ejection fraction attending the Benjamin Mkapa hospital in Dodoma, Tanzania.

## Materials and methods

### Study objectives

To determine the prevalence of cardiorenal anemia syndrome among patients with heart failure attending a tertiary referral hospital in Dodoma, TanzaniaTo determine the clinical correlates of cardiorenal anemia syndrome among patients with heart failure attending a tertiary hospital in Dodoma, TanzaniaTo determine the outcomes of cardiorenal anemia syndrome among patients with heart failure attending a tertiary referral hospital in Dodoma, Tanzania

### Study design

A hospital based prospective observational study.

### Study duration

Study is conducted for 9 months period start from 18^th^ August, 2023 to 18^th^ April, 2024. Recruitment is from 18^th^ August, 2023 to 18^th^ October, 2023 and follow-up period will commence a month later after recruitment up to 6 months. Last patient will followed up to 18^th^ April, 2024.

### Study settings

This study is ongoing at the Benjamin Mkapa Hospital (BMH). This is a government tertiary hospital that serves as a national consultant hospital located in the capital city of Tanzania. The hospital is located within the University of Dodoma (UDOM) premises, 13 kilometres from Dodoma city center. It was established in 2015 and named in remembrance of Former third President, His Excellence Benjamin William Mkapa. This hospital serves a population of Dodoma of about 3.08 million as per Tanzania demographic health survey (TDHS) report published in 2022 [15] and other inhabitants from neighbouring regions of Iringa, Singida, Manyara, Tabora, Morogoro, and Katavi [16]. The hospital has bed capacity of 400. The BMH serves as a teaching hospital for the University of Dodoma for both undergraduate and graduate programs.

### Study population

Patients (Human subjects) with heart failure who met inclusion criteria will be recruited.

#### Inclusion criteria

All patients aged ≥ 18 years oldPatients with heart failure irrespective of ejection fraction with echocardiographic report within 6-months prior enrollment.Patients with chronic heart failure who will undergo echocardiographic imaging during index contactPatients admitted with a confirmed index diagnosis of acute heart failurePatients with either baseline evidence of chronic kidney disease from medical records within 6-months prior enrollment or new patient with chronic kidney disease based on serum creatinine level during index contactPatient who has signed the informed consent form or proxy consent incase the patient is incapable

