### Sample size estimation

To estimate the sample size, the proportionate formula used in prospective cohort studies will be used as it has been adopted from Baraka et al., 2023 [16].

$$n={\frac{\left(Z_{\alpha }/2\sqrt{\left(\frac{r+1}{r}\right)p*\left(1-p*\right)}+Z_{\beta }\sqrt{\frac{p_{1}\left(1-p_{1}\right)}{r}p_{2}\left(1-p_{2}\right)}\right)}{{\left(p_{1}-p_{2}\right)}^{2}}}^{2}$$

$$p*=\frac{p_{2}+rp_{1}}{r+1}$$

Where by

r = ratio between the two groups

p1 = CRAS prevalence obtained from literature

p2 = expected prevalence of CRAS from the study

p1 –p2 = effect size

Zβ = standard normal variate for statistical power

Zα/2 = standard normal variate for significance level

The prevalence of CRAS in previous studies was 44.4% [2]

The prevalence of CRAS in this study is expected to be 40%

Therefore;

r = 1

p1 = 44.4%

p2 = 40%

p1 − p2 = 13%

Zβ = 0.84 for statistical power of 80%

Zα/2 = 1.96 for significance level of 95%

n = 226

Considering the 30% attrition rate adopted from previous study [2]

Therefore, the minimum sample size required to meet the objectives will be 300 patients.

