### Clinical outcomes

#### Primary outcome

Cardiorenal anemia syndrome (CRAS) is the primary outcome of this study and will be defined as a triad comprising heart failure regardless of ejection fraction, chronic kidney disease with estimated glomerular filtration rate <60mil/min/1.73m^2^ and anemia of <12 g/dl for women or <13 g/dl for men [1, 2].

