**Chronic kidney disease (CKD)**	Medical records/patient report	Known patient with CKD from medical records within 6 months retrospectively prior enrollment or when estimated GFR is <60mil/min/1.73m2 by CKD-EPI formula using serum creatinine level	Dichotomous, continous
**Dyslipidemia**	Medical records/patient report/blood sample	Evidence of dyslipidemia on medications from records or for unknown lipid status, when the total cholesterol ≥200 mg/dl, low-density lipoprotein cholesterol ≥130 mg/ dl, and high-density lipoprotein cholesterol < 40 mg/ dl for men or < 50 mg/ dl for women, and/or serum triglyceride level ≥150 mg/ dl	Dichotomous, categorical
**Diabetes**	Medical record/patient report/blood sample	Known patient with diabetes mellitus on medications from records or for unknown status, is when the random blood glucose is ≥11.1 mmol/L and glycosylated haemoglobin of ≥6.5%	Dichotomous, categorical
**Electrolyte imbalance**	Medical report/blood sample	Serum Na+ of <135mmol/L or >145mmol/L and/or serum K+ of < 3.5mmol/L or >5.5mmol/L	Continous
**Obesity**	Medical record/patient assessment	When the waist circumference of >94 cm for males or >88 cm for females; or calculated waist-hip ratio (WHR) of >0.9 for men or of >0.8 for women	Dichotomous, categorical

#### Objective 3

Aims to determine the outcomes of the cardiorenal anemia syndrome among the patients with heart failure within six months follow up period [2, 5, 7, 11, 25] Table 3.

**Table 3 pone.0292764.t003:** Summary and description of variables for the objective number 3.

Variable	Method of measurement	Operational definition	Level of measurement
**All-cause mortality**	Medical records or close relative through phone contact	Any death occurs within six month follow up irrespective of the cause of death	Dichotomous
**Heart failure hospitalization**	Medical record/patient report/assessment	admission of which cause-specific is heart failure	Continuous
**Worsening renal function**	Medical record/patient report/blood sample	When there is a change in Chronic kidney disease stage or a need of dialysis or both	Continuous
**Worsening anemia**	Medical record/patient assessment/blood sample	Change of hemoglobin level to lower level from baseline or a need of blood transfusion or erythropoietin use or both	Continuous

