### Data analysis

All completed questionnaires will be coded before entered into dataset on Microsoft excel. SPSS windows version 25 program (IBM SPSS, Chicago IL) will be used for data management and analysis [16]. Data will be classified as CRAS or non-CRAS groups. Data will be presented as means **±** standard deviations for continuous variables with normal distribution, or median and interquartile range for no-parametric (skewed) variables [1, 2, 13]. Categorical variables will be presented as frequencies and percentages. Socio-demographic variables and clinical correlates of cardiorenal anemia syndrome at baseline will be analyzed and compared using Pearson chi-squared test for the categorical variables, and independent student’s t-test for the continuous variables [1, 2, 9]. The clinical correlates including age, gender, alcohol use, smoking history, hypertension, obesity, diabetes, and dyslipidemia and iron deficiency will be analysed and compared by using univariate and multivariate logistic regression. Cox proportional hazards model will be used to analyze and compare the outcomes of CRAS. A two-tailed p—value of less than 0.05 will indicate statistical significance [2, 7, 13].

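### Read naturally, the inclusion list admits only heart failure patients who already have chronic kidney disease, which conflicts with the aim of CRAS prevalence and correlates among heart failure patients

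*Protocol article*

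**What the plan says.** Study objectives sets the first aim as "To determine the prevalence of cardiorenal anemia syndrome among patients with heart failure attending a tertiary referral hospital in Dodoma". The text for objectives 1 and 2 under Study variables repeats heart failure, at any ejection fraction, as the population. Neither section restricts by kidney function.

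Primary outcome defines CRAS as a "triad comprising heart failure regardless of ejection fraction, chronic kidney disease with estimated glomerular filtration rate" below 60, together with anaemia.

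Inclusion criteria lists age, three heart failure items (a recent echo report, chronic heart failure with an echo at the index contact, admission with acute heart failure), a kidney item and consent. The kidney item reads: "either baseline evidence of chronic kidney disease from medical records within 6-months prior enrollment or new patient with chronic kidney disease based on serum creatinine". No connecting words say which items are alternatives and which are required.

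Study population says "Patients (Human subjects) with heart failure who met inclusion criteria will be recruited".

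Table 2 under Study variables lists CKD as a dichotomous (and continuous) variable. Its definition is close to the entry item: "Known patient with CKD from medical records within 6 months retrospectively prior enrollment or when estimated GFR is" below 60.

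Data analysis states "Data will be classified as CRAS or non-CRAS groups". It then applies logistic regression to the correlates and a Cox model to the outcomes.

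**The concern.** One of the three components that define the primary outcome also appears among the conditions for entry. If it is applied as a condition, a heart failure patient with normal creatinine is turned away, and the denominator named in objective 1 is not the one sampled.

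All three objectives would be affected:

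- **Objective 1** would approximate the proportion anaemic among patients with heart failure and CKD.
- **Objective 2** would compare anaemic with non-anaemic patients inside that group. Factors that may act through kidney disease, such as hypertension and diabetes, could look weaker than they are, because the comparator contains no heart failure patients with normal kidneys.
- **Objective 3** would likewise contrast outcomes by anaemia within heart failure plus CKD, not the syndrome with its absence.

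Analysis could not repair this afterwards. The article describes no count of heart failure patients without CKD and no screening denominator.

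**Working it through.** **Reading the list.** The three heart failure items must be alternatives, since no patient need satisfy all of them. Age and consent are plainly required. The kidney item is separate, stands beside those two, and spells out two ways of being met (records or index creatinine). With Study population recruiting heart failure patients who meet the list, the natural reading is heart failure and CKD.

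**Against the other sections.** The objectives name heart failure patients without a kidney restriction. Table 2 gives CKD as dichotomous, but under the natural reading nearly every entrant would have the same value. Both conflict with that reading of the list.

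**What would be measured.** Write HF for heart failure and take probabilities among otherwise eligible patients.

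- P(CRAS | HF) = P(CKD | HF) × P(anaemia | HF, CKD).
- If every entrant has CKD, the measured proportion is P(anaemia | HF, CKD) = P(CRAS | HF) / P(CKD | HF).
- The two agree only if P(CKD | HF) = 1.

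**Inputs.** Sample size estimation says "The prevalence of CRAS in this study is expected to be 40" per cent. This is an input to the protocol, so there is no derivation of it to reproduce. P(CKD | HF) is not in the documents; I assume 0.5 to 0.8.

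**Ratio of measured to heart-failure-wide prevalence:** 1 / 0.8 = 1.25; 1 / 0.5 = 2.

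**If 40% is observed in an all-CKD sample**, the heart-failure-wide value is:

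- 0.40 × 0.5 = 0.20
- 0.40 × 0.8 = 0.32

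**If instead 40% were the heart-failure-wide value**, an all-CKD sample would show:

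- 0.40 / 0.8 = 0.50
- 0.40 / 0.5 = 0.80

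**Limit of the formula.** CKD taken from records need not mean eGFR below 60 at baseline. Some entrants could be non-CRAS for renal reasons. They add to the denominator but not to the cases, so the measured proportion would be somewhat lower than the formula gives. The relation is approximate.

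**The case against.** The best defence is that the kidney item was never meant as a condition. It has the same form as the echo items (recent records or index contact), so it may only describe how CKD status is ascertained. Table 2 uses nearly the same wording for a variable expected to vary, and no objective mentions a CKD restriction. On that reading Study population still requires heart failure and the intended denominator is kept. This is a possible intention, and it is why the point cannot be put as a certainty. It does not remove the conflict: the item sits in the list of entry criteria, and a recruiter applying the list would exclude patients with normal kidneys.

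A reader might infer more than the documents support:

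- **That every reading of the list gives the wrong population**, because the item could admit CKD patients without heart failure. Study population blocks this, and Evaluation of the participants adds a modified Framingham diagnosis of heart failure. Recruiting from the nephrology department, under Participants' characteristics, does not change that, nor does it show that patients without CKD are refused.
- **That the study will report 57% to 80% in place of a true 40%**, from assumed CKD shares of 0.7 to 0.5. The 40% is the figure expected in this study, so under the restrictive reading it may already be the restricted figure. It cannot be taken as a heart-failure-wide value.
- **That the comparison with published figures is invalid.** Sample size estimation says "The prevalence of CRAS in previous studies was 44.4" per cent without saying whether that denominator was restricted to CKD. Comparability is unknown, not disproved.

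**Conclusion.** The point holds as an unreconciled conflict between the eligibility list and the objectives. On the natural reading, two of the three CRAS components are fixed at entry. The study would then estimate roughly the prevalence, correlates and outcomes of anaemia among patients with heart failure and CKD. On the ascertainment reading the heart failure denominator survives, but the text does not say that this is meant.

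The size can only be illustrated. Over an assumed CKD share of 0.8 to 0.5, the measured proportion is about 1.25 to 2 times the heart-failure-wide prevalence. This rests on the kidney item being enforced, on the assumed share, and on entry CKD being close to eGFR below 60. How the item was applied to the 92 patients already recruited is not stated.

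**What to change.** 1. Remove CKD as an entry condition. Classify it after enrolment from the index serum creatinine, which Laboratory and imaging investigations already lists among the blood tests. If the item was only meant to say how CKD is ascertained, move it to the variable definitions and say so.
2. Check how the 92 patients already recruited were screened.
3. If the item was enforced, either report the patients enrolled under it separately, or restate the objectives as prevalence, correlates and outcomes of anaemia among patients with heart failure and CKD. Do not present that figure as CRAS prevalence in heart failure.

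**Cost.** A short amendment and a check of screening records; no new test is needed. Opening entry to all heart failure patients gives fewer CRAS cases per 300 enrolled. As an illustration, if 40% applied to an all-CKD sample, 300 × 0.40 = 120 cases would become 300 × 0.20 = 60 to 300 × 0.32 = 96. A change during recruitment also leaves two entry rules to separate in the analysis. Restating the objectives avoids both costs but gives up the question the study set out to answer.

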#### Exclusion criteria

Patients with known solid or hematological malignancy on chemotherapy or radiotherapyPregnant womenPatients with obvious gastrointestinal bleeding from any causePatients with established Hemoglobinopathies or other non-gastrointestinal bleeding disordersPatients with known history of Chronic kidney disease stage 5 on iron supplementation, or on renal replacement therapyPatients underwent implantable cardiac devices or pacemaker implantation

### Sample size estimation

To estimate the sample size, the proportionate formula used in prospective cohort studies will be used as it has been adopted from Baraka et al., 2023 [16].

$$n={\frac{\left(Z_{\alpha }/2\sqrt{\left(\frac{r+1}{r}\right)p*\left(1-p*\right)}+Z_{\beta }\sqrt{\frac{p_{1}\left(1-p_{1}\right)}{r}p_{2}\left(1-p_{2}\right)}\right)}{{\left(p_{1}-p_{2}\right)}^{2}}}^{2}$$

$$p*=\frac{p_{2}+rp_{1}}{r+1}$$

Where by

r = ratio between the two groups

p1 = CRAS prevalence obtained from literature

p2 = expected prevalence of CRAS from the study

p1 –p2 = effect size

Zβ = standard normal variate for statistical power

Zα/2 = standard normal variate for significance level

The prevalence of CRAS in previous studies was 44.4% [2]

The prevalence of CRAS in this study is expected to be 40%

Therefore;

r = 1

p1 = 44.4%

p2 = 40%

p1 − p2 = 13%

Zβ = 0.84 for statistical power of 80%

Zα/2 = 1.96 for significance level of 95%

n = 226

Considering the 30% attrition rate adopted from previous study [2]

Therefore, the minimum sample size required to meet the objectives will be 300 patients.

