### Data collection process

#### Evaluation of the participants

A minimum of 300 patients who meet the inclusion criteria will be enrolled in this study from 18^th^ August, 2023 to 18^th^ April, 2024 including 3-months of enrollment and a 6-month of follow up. Follow-up period will be done on monthly basis via phone calls or through routine clinic visits to assess for the secondary outcomes. Data will be collected using a well-structured questionnaire, which will include socio-demographic information, physical examination and anthropometry, assessment of underlying comorbid conditions, laboratory investigations, and non-invasive cardiac imaging. Socio-demographic data will include age, gender, smoking history, history of alcoholic use either current or previous case, and anthropometric measurements including waist circumference, hip circumference and then, waist-hip ratio will be calculated [28]. Focused clinical history will be exhausted to assess the symptoms related to heart failure using modified Framingham criteria. Two major criteria or one major and two minor criteria will be sufficient to make a diagnosis of heart failure [29]. Subjective Functional status by using New York Heart Association functional criteria will be recorded, which comprises four classes as follows [2, 12, 30]: class 1 means no limitation to physical activities, class 2 means slight limitation to strenuous activities, class 3 means marked limitation to simple and slightly activities and class 4 means symptoms at rest.

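### Enrolling 300 does not keep 226 patients after 30% attrition: it leaves 210, and the allowance bears only on the six-month outcomes

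*Protocol article*

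**What the plan says.** Under Sample size estimation, the protocol article uses a two-group formula for proportions with r = 1, p1 = 44.4% (CRAS prevalence in earlier work), p2 = 40% (CRAS prevalence expected here), a difference printed as 13%, "Zβ = 0.84 for statistical power of 80"% and "Zα/2 = 1.96 for significance level of 95"%. The result is n = 226. The attrition step follows: "Considering the 30% attrition rate adopted from previous study [2"]. The conclusion is: "Therefore, the minimum sample size required to meet the objectives will be 300 patients". No formula is printed for the step from 226 to 300.

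Under Evaluation of the participants, 300 is the number enrolled, not the number completing: "A minimum of 300 patients who meet the inclusion criteria will be enrolled in this study".

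On timing, the abstract places prevalence and correlates at baseline, and the Study variables section does the same for objectives 1 and 2. For objective 3 the abstract says that "the outcomes of CRAS will be determined during a follow-up period of six months from the date of enrollment". The Follow-up procedure section sets monthly contact and a rule for declaring a patient lost. The Data analysis section assigns the outcomes to a Cox proportional hazards model.

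**The concern.** An attrition rate is normally the share of enrolled patients who are later lost. An allowance for it should give an enrolment figure that still leaves the required number once that share is removed. Here it does not: taking 30% off 300 gives a number below 226. A figure labelled a minimum therefore fails under the loss rate stated immediately before it.

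The allowance is also stated for the objectives as a whole. Loss during follow-up cannot reduce an analysis of baseline prevalence or baseline correlates, so it belongs to objective 3 alone. Two things are at stake. A reader is told that the design covers 30% loss when it covers less. And if the same inflation method is used when the base figure is recomputed, the shortfall will carry over to the new figure.

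**Working it through.** **Inputs.** From Sample size estimation: base n = 226; attrition d = 0.30; final figure 300; p1 = 0.444; p2 = 0.40; printed difference 0.13; r = 1; z values 1.96 and 0.84. From Evaluation of the participants: 300 is the number enrolled. From Data analysis: a two-tailed test, where a p-"value of less than 0.05 will indicate statistical significance".

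**Step 1: reproduce the base figure.** The standard pooled formula for two proportions with r = 1 is

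n = [1.96 √(2 p*(1 − p*)) + 0.84 √(p1(1 − p1) + p2(1 − p2))]² / difference²

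with p* = (0.444 + 0.40)/2 = 0.422.

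- First term: 1.96 × √(2 × 0.422 × 0.578) = 1.96 × 0.6985 = 1.369
- Second term: 0.84 × √(0.2469 + 0.2400) = 0.84 × 0.6978 = 0.586
- n = (1.369 + 0.586)² / 0.13² = 3.822/0.0169 = 226.2

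So 226 reproduces, with the printed 13% as the difference. Both proportions are CRAS prevalences.

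**Step 2: how 300 may have been reached.** 226 × (1 + 0.30) = 293.8, which is consistent with 300 after rounding up. This route is an inference. The steps below do not depend on it.

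**Step 3: what 300 delivers under 30% loss.** 300 × (1 − 0.30) = 210. Shortfall: 226 − 210 = 16, and 16/226 = 7%.

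**Step 4: what would keep 226.** 226/(1 − 0.30) = 322.9, so 323, which is 23 more than 300. Check: 323 × 0.70 = 226.1.

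**Step 5: the loss that 300 can absorb.** (300 − 226)/300 = 74/300 = 24.7%.

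**Step 6: does the fault carry over?** Multiplying by 1.30 and then losing 30% leaves n × 1.30 × 0.70 = 0.91n, a 9% shortfall at any n. Here rounding 293.8 up to 300 reduces it to 7%.

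**Step 7: which objectives it touches.** Objectives 1 and 2 are fixed at enrolment, so all 300 count. Objective 3 runs over six months, so 210 is the expected number of completers there under the stated rate.

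**The case against.** The strongest reply is that no objective, as the protocol defines it, misses a target. The 226 was derived from two CRAS prevalences, CRAS is the primary outcome, and it is determined at baseline. That analysis has all 300 patients. Objective 3 could fall to 210 completers, but no requirement of 226 was ever derived for it. This stands, and it limits the point to a misstated figure.

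A reader might infer that the mortality, hospitalization, renal and anemia comparisons would rest on only 210 patients. The documents do not support that. The outcomes go to a Cox model, in which patients contacted monthly and then lost would ordinarily contribute time until censoring. Table 3 also allows deaths to be ascertained from medical records or by telephone from a relative. The 210 is a count of complete follow-up, not the number analysed.

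The reply can add that the gap is small. If 226 and 210 are read as group sizes for 44.4% against 31.4% (the printed 13 points taken off p1, not the pair of rates in the protocol), power is about 82% and 79%. The 300 is also described as a floor. Both remarks are fair on size, but neither makes the three printed figures agree.

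Finally, the effect size is a larger fault in the same section: 44.4% − 40% is 4.4 points, not 13. With 4.4 points the formula in Step 1 gives 3.822/0.001936, about 1,975 per group. The 226 is likewise a per-group result of a two-group formula, used as a total. These are separate faults. They mean that 323 should not be taken as a valid sample size, but they do not correct the attrition step.

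**Conclusion.** The point holds as a matter of stated figures. With 30% attrition, 300 enrolled leaves 210, not 226. Keeping 226 would take 323, and 300 covers loss of up to 24.7%. This rests on reading 30% as the share of enrolled patients lost and 300 as the number enrolled. The second is explicit in the article, and the article offers no other meaning for the first.

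The consequence is modest. Objectives 1 and 2 are unaffected. For objective 3, about 210 of 300 would be expected to have complete six-month follow-up, with the others contributing censored time. No loss of power against a stated objective 3 requirement can be shown, because the article derives none. The correction is still worth making: the minimum is wrong under its own assumption, and the same step would leave any recomputed figure short.

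**What to change.** Amend the end of Sample size estimation as follows.

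- Keep 300, and say either that it allows for just under 25% loss relative to 226, or that about 210 patients are expected to complete six months if 30% are lost.
- State that objectives 1 and 2 use all enrolled patients and that attrition applies only to objective 3.
- When the base figure is recomputed after the 13% versus 4.4-point discrepancy is corrected, divide by (1 − attrition) and print that step.

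Replacing 300 with 323 alone is not advised, since it would refine a base figure that is itself in question.

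Cost: a few sentences and no extra patients. The downside is a slightly less favourable stated figure for the follow-up objective.

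### The sample size calculation enters a 13-point difference where its own inputs differ by 4.4 points, so the 80% power claimed for 300 patients is not delivered

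*Protocol article*

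**What the plan says.** All inputs stand in the protocol article under Sample size estimation. A two-proportion formula is used, with "r = ratio between the two groups" set to 1. The first proportion, p1, is the CRAS prevalence from the literature, 44.4%. For the second, p2, the text says "The prevalence of CRAS in this study is expected to be 40" per cent. The effect to be detected is defined as a plain difference: "p1 –p2 = effect size". The next list of values gives p1 − p2 as 13%.

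The error rates are "Zβ = 0.84 for statistical power of 80" per cent and "Zα/2 = 1.96 for significance level of 95" per cent, the latter evidently meaning a two-sided 5% level. The result is n = 226. Then follows "Considering the 30% attrition rate adopted from previous study", and the conclusion "Therefore, the minimum sample size required to meet the objectives will be 300 patients". The section on evaluation of the participants repeats 300 as the minimum for the whole study.

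**The concern.** A difference defined as p1 − p2 cannot be 13% when p1 is 44.4% and p2 is 40%. If 13% were only a misprint in the text, the stated n would still follow from the correct difference. If it went into the calculation, then n = 226, the 80% power and the minimum of 300 all rest on an effect about three times the one the inputs describe (13/4.4 = 2.95). A reader would then credit the study with a power it does not have, and could over-read a comparison that shows no difference.

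There is also a question of purpose. The calculation contrasts a published prevalence with this study's prevalence. The objectives are to estimate a prevalence, to find its correlates and to compare outcomes, and it is not clear that the calculation serves any of them.

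**Working it through.** **Inputs** (Sample size estimation): p1 = 0.444, p2 = 0.40, r = 1, Z = 1.96 and 0.84, entered difference 0.13, attrition 30%.

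**Formula.** The printed formula shows a product under the second square root and a misplaced square, which may be a fault of text extraction. The standard form for r = 1 is

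n per group = [1.96·√(2p*(1−p*)) + 0.84·√(p1(1−p1) + p2(1−p2))]² / (p1−p2)², with p* = (p1+p2)/2 = 0.422.

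**Step 1: reproduce the plan's figure.**
- First term: 1.96·√(2 × 0.422 × 0.578) = 1.96·√0.4878 = 1.369
- Second term: 0.84·√(0.2469 + 0.2400) = 0.586
- Squared sum: (1.369 + 0.586)² = 3.822
- With the entered difference: 3.822 / 0.13² = 226.2, the stated 226
- With the product under the root, as printed: about 146, not 226

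So 226 came from the standard form, with 44.4% and 40% in the variance terms and 0.13 in the denominator.

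**Step 2: use the difference the inputs give.** 0.444 − 0.40 = 0.044, and 3.822 / 0.044² = 1,974 per group. The product form gives 1,279, also far from 226.

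**Step 3: can 13% be explained?** It is not a relative difference of the same inputs: 4.4/44.4 = 9.9% and 4.4/40 = 11%. If 13 points was meant and one prevalence is misprinted, the formula gives these sizes per group:
- 44.4% vs 31.4%: 218
- 44.4% vs 57.4%: 231
- 40% vs 27%: 206
- 40% vs 53%: 230

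None is 226. No other section gives a source for 13%.

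**Step 4: power for 44.4% vs 40%, two-sided 5%.** For n per group, power = Φ{[0.044 − 1.96·√(0.4878/n)] / √(0.4869/n)}. For one sample against a fixed 44.4%, power = Φ{[0.044·√n − 1.96·√(0.444 × 0.556)] / √(0.40 × 0.60)}.

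| Reading | Power |
|---|---|
| 226 per group | Φ(−1.01) = 16% |
| 300 per group | Φ(−0.87) = 19% |
| 300 split into two groups of 150 | Φ(−1.19) = 12% |
| One sample of 300 against a fixed 44.4% | Φ(−0.43) = 33% |

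**Step 5: attrition.** 300 × 0.70 = 210, below 226. To keep 226 after 30% loss needs 226 / 0.70 = 323.

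**Step 6: link to the analysis.** The Data analysis section plans chi-squared and t-tests, logistic regression and Cox models on CRAS versus non-CRAS. It plans no test of this study's prevalence against a published one. CRAS status is determined at baseline (Abstract; Study variables, Objective 1), so loss during follow-up does not reduce the prevalence sample. Attrition matters for the six-month outcomes of Objective 3.

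**Step 7: what 300 does deliver.** For prevalence, the 95% half-width is 1.96·√(0.40 × 0.60/300) = 0.055, or 0.056 at 44.4%. For outcomes, take 210 patients with complete follow-up, split 40/60 into 84 CRAS and 126 non-CRAS, with 80% power. The protocol gives no non-CRAS event rate, so a range is assumed:

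| Assumed non-CRAS rate | Detectable CRAS rate |
|---|---|
| 10% | about 25% |
| 20% | about 38% |
| 30% | about 49% |

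This is a two-proportion approximation to the planned Cox analysis.

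**The case against.** The contradiction itself has no good defence: it is not blacked-out text, and no misprinted prevalence gives 226 exactly. Several wider readings are open to challenge, and most of those challenges stand.

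- **Per-group n used as a total.** A reader might infer that 226 had to be doubled to 452. The protocol defines its groups as the literature and this study, so only one group is enrolled, and 226 could be the number to recruit here. The doubling applies only if two groups are to be drawn from the enrolled patients, which the section does not say. The 12% figure carries the same condition.
- **How 226 became 300.** A reader might infer 226 × 1.3 = 294, rounded up. The protocol does not show that step. Only the result can be stated: 300 leaves 210 after the assumed loss.
- **Allowing for attrition at all.** The minimum is tied to the objectives as a whole, and one of them is a six-month follow-up, so an allowance is reasonable for the study. It is simply irrelevant to the baseline prevalence.
- **Detectable differences.** The Cox model uses patients until they are censored, so 210 is not strictly the analysis set, and the event rates are assumed. Hence the range and the label of approximation.
- **Is 300 too few?** A reader might infer that the study needs thousands of patients. The documents do not support that. The prevalence objective is descriptive, no test against 44.4% is planned, and nothing shows 300 to be inadequate for estimating a prevalence.

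**Conclusion.** The point holds for the justification of the sample size. The difference entered is 13 points, the inputs give 4.4, and the wrong value produced n = 226. For the stated prevalences the formula needs 1,974 per group. Power with 300 patients runs from about 12% to 33% across the readings considered, so the claimed 80% fails under each of them. Separately, 300 does not preserve the document's own 226 after 30% loss, and the contrast used is not one that the analysis tests.

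These results assume a two-sided 5% level, the normal approximation, and the standard formula in place of the printed one. The first agrees with the Data analysis section, and the last is supported by its exact reproduction of 226. The conclusion does not extend to 300 being unsuitable as a prevalence sample.

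**What to change.** 1. Reconcile p1, p2 and their difference, and correct the printed formula if the product under the root is in the source.
2. Withdraw the 80% power claim and the statement that this calculation makes 300 the required minimum.
3. Keep 300 and justify it by precision: at an expected CRAS prevalence of 40%, 300 patients give a 95% confidence interval of about ±5.5 percentage points. Name the population to which this applies. The inclusion criteria list chronic kidney disease; if that is required of every participant, the estimate does not describe heart failure patients in general.
4. Apply attrition to the outcome objective only. State that about 210 patients with complete follow-up (40/60 split, 80% power) can detect roughly 10% vs 25%, 20% vs 38% or 30% vs 49%, labelled as assumed non-CRAS rates and as a two-proportion approximation to the Cox analysis.

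The cost is the rewording of one section, with no extra patients and no change to conduct. The drawback is that the stated figures become less favourable: a precision statement and fairly large detectable differences replace a claim of 80% power.
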